| 2. Duration of moderately bad (or worse) symptoms                                                                                                                                       | Last day on which any symptom was recorded as “moderately bad” or worse                                                                                                                                                                                                                                                                                                                                                                                              | Trial Diary  completed daily by participant               |
| 3. Time to return to usual activities                                                                                                                                                   | 
Length of time to return to usual activities. This will be defined as per the ALICE trial:
 
 
Participants ≥16 years as the last day on which they mark “Unable to do usual activities” AND “Fever” as no more than “slight problem”.
 
Children <16 year as the last day on which they mark “Child not themselves/more clingy than usual” AND “Fever” as no more than “slight problem”
 
 | Trial Diary  completed daily by participant               |
| 4. Overall symptom duration                                                                                                                                                             | Last day prior to all symptoms recorded as zero for two consecutive days                                                                                                                                                                                                                                                                                                                                                                                             | Trial Diary  completed daily by participant               |

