### **6.9 Follow-Up**

The Trial Diary will be completed daily by the participant until their symptoms resolve (defined as all symptoms being rated zero for two days in a row) or up to day 28, whichever comes first. The central trial team will contact participants regularly via email, text or phone to support completion of the Trial Diary. Completed paper versions of the Trial Diary should be returned to BTC. Participants will be advised that if their symptoms have not resolved by Day 28, or if they have any concerns before Day 28, they should contact their GP practice for further advice.

Participants (or parent/carer if the participant is <16 years) will be followed-up with a questionnaire at 2 months post-randomisation which will collect beliefs and intention to consult for similar future illnesses (see Appendix 1, Participant Views questions 6 and 7). Up to two reminders will be sent for cases where the questionnaires are not returned. Questionnaires may be completed with the participants over the phone, and the data entered by the central trials team, if required. In addition, data on any further GP consultations for RTIs will be collected from their PCMR at 2- and 6- months after randomisation. For those participants randomised in the later stages of Summer 2, there will be a shorter follow-up period to ensure that all follow-up is completed 2 months after recruitment has finished.

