### 2.10.2. CLINICAL SECONDARY OUTCOMES

**Participant-completed symptom diaries** at baseline (day 1, pre-randomisation) and for 28 days afterwards (first post-randomisation completion on day 1 after appointment 2). Ten symptoms were completed by all participants: blocked nose, fever, shortness of breath, phlegm, wheeze, eating or drinking less than normal, disturbed sleep, ear pain and change in voice. Those age 16+ years completed four further symptoms: sore throat, muscle facial or head aching or pain, sweats or chills, and unable to do usual activities e.g. work school childcare etc. Those age under 16 years completed one additional item: child not themselves or more clingy than usual. Each item was responded to using the following seven-point scale:

- 0 = Normal/not affected
- 1 = Very little problem
- 2 = Slight problem
- 3 = Moderately bad
- 4 = Bad
- 5 = Very bad
- 6 = As bad as it could be

Participants are instructed to stop completing the diary once they have two consecutive days for which all symptoms are rated at zero, or once 28 days have been completed.

For any diary days that have been partially completed, with at least one symptom completed, symptoms left blank will assumed to be scored as zero (i.e. the symptom is completely resolved). Any days with no symptoms rated will be considered as missing data.

In addition participants were asked to record in the daily diaries if they were taking an antibiotic, which one, and how many doses were taken each day.

The following measures were derived from participant-completed symptom diaries:

| Diary measures                                                                         | Type       | Outcome detail                                                                                                                                                                                                                                                                                                                               |
|----------------------------------------------------------------------------------------|------------|----------------------------------------------------------------------------------------------------------------------------------------------------------------------------------------------------------------------------------------------------------------------------------------------------------------------------------------------|

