| Mean symptom severity on days 2 to 4
(KEY SECONDARY OUTCOME)                        | Continuous | Each day's responses will be converted to a mean score = sum of responses divided by the listed number of symptoms.                                                                                                                                                                                                                          |
| Duration of moderately bad (or worse) symptoms                                         | Ordinal    | Longest continuous spell (in days) with one or more symptoms rated $\geq 3$ , concluding with two days where all symptoms are rated $< 3$ .                                                                                                                                                                                                  |
| Number of days to return to usual activities (adult participants $\geq 16$ years only) | Ordinal    | For participants with "Unable to do usual activities" rated $\geq 3$ at baseline, the number of consecutive days that item is rated $\geq 3$ , followed by two days where it is rated $< 3$ . For participants with "Unable to do usual activities" rated as $< 3$ at baseline, their duration will be zero.                                 |
| Number of days to return to usual activities (child participants $< 16$ years only)    | Ordinal    | For participants with "Child not themselves / more clingy than usual" rated $\geq 3$ at baseline, the number of consecutive days that item is rated $\geq 3$ , followed by two days where it is rated $< 3$ . For participants with "Child not themselves / more clingy than usual" rated as $< 3$ at baseline, their duration will be zero. |
| Overall symptom duration                                                               | Ordinal    | The number of consecutive days one or more symptoms are rated $> 0$ , concluding with two days where all symptoms are rated 0.                                                                                                                                                                                                               |

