| Other symptom measures                           | Mean (SD), n                 | Mean (SD), n            | Difference in meansc
(95% confidence interval) | P value |
| Duration of moderately bad, or worse, symptoms          | X.X (X.X), X                        | X.X (X.X), X                   | XX.XX (XX.XX, XX.XX)                                                 | 0.XXX          |
| Time to return to usual activities (adults 16+ years)   | X.X (X.X), X                        | X.X (X.X), X                   | XX.XX (XX.XX, XX.XX)                                                 | 0.XXX          |
| Time to return to usual activities (children <16 years) | X.X (X.X), X                        | X.X (X.X), X                   | XX.XX (XX.XX, XX.XX)                                                 | 0.XXX          |
| Overall symptom duration                                | X.X (X.X), X                        | X.X (X.X), X                   | XX.XX (XX.XX, XX.XX)                                                 | 0.XXX          |
|                                                         | n/N (%)                      | n/N (%)                 | Odds ratioa
(95% confidence interval)          | P value |
| Participant experiences worsening symptoms              | XX/XXX (XX%)                        | XX/XXX (XX%)                   | XX.XX (XX.XX, XX.XX)                                                 | 0.XXX          |

a. All estimates adjusted for participant age and chronic lung disease status

b. One-sided 95% confidence interval, for establishing non-inferiority, presented in the text

c. Bias-corrected and accelerated bootstrap confidence intervals, non-parametric p-value

**Table 4.** Further healthcare contacts post-randomisation

|                                                                                                  |    | Intervention
N (%) | Control
N (%) | Odds ratio*
(95% confidence interval) | P value* |
|--------------------------------------------------------------------------------------------------|----|-----------------------|------------------|------------------------------------------|----------|
| Number (%) of patients hospitalised for RTI one or more times between appointment two and day 28 |    | XX (XX%)              | XX (XX%)         | XX.XX (XX.XX, XX.XX)                     | 0.XXX    |

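### The SAP gives no value to symptom spells still open at Day 28 or at diary stop, and its duration rules lose relapse and later impairment that the protocol's definitions would count

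*Combined protocol and SAP*

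**What the plan says.** SAP 2.10.2 derives three kinds of duration from the diary:

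- **Moderately bad symptoms:** "Longest continuous spell (in days) with one or more symptoms rated" 3 or more, ended by two days with every symptom below 3.
- **Overall duration:** consecutive days with any symptom above zero, "concluding with two days where all symptoms are rated 0".
- **Return to usual activities:** consecutive days with the relevant item at 3 or more, followed by two days below 3. For participants below 3 "at baseline, their duration will be zero".

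On diary completion, the same section says: "Participants are instructed to stop completing the diary once they have two consecutive days for which all symptoms are rated at zero", or after 28 days. It adds: "Any days with no symptoms rated will be considered as missing data".

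SAP Table 3 reports these durations as differences in means. Its footnote c specifies "Bias-corrected and accelerated bootstrap confidence intervals, non-parametric p-value". SAP 4.7 otherwise leaves the regression model open. The missing-data sensitivity analysis in SAP 4.6 (item 3) covers the key secondary outcome only.

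Protocol Table 1 defines the moderately bad outcome differently: "Last day on which any symptom was recorded as" moderately bad or worse. Its usual-activities outcome combines the activity item with fever and has no rule that sets the value to zero from the baseline rating.

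For late Summer 2 recruits, protocol 6.9 says "there will be a shorter follow-up period to ensure that all follow-up is completed 2 months after recruitment has finished".

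**The concern.** A duration that exists only once a closing pair of days has been seen has no value for a participant still ill on Day 28, or for one who abandons the diary while ill. These include the longest illnesses. Leaving them out selects on the outcome after randomisation, and a comparison of means among closed spells moves towards no difference.

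Two further rules change what is measured. The longest spell ignores a relapse that is shorter than the first episode. The baseline rule gives zero days to someone who was coping at presentation but became unable to function on, say, Day 3.

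The trial aims to reduce antibiotic prescribing, so how long patients stay ill is part of the evidence on whether that is acceptable. Two analysts following this SAP could report different duration results from the same diaries.

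**Working it through.** **The plan's own figure.** No size or power is stated for the duration outcomes. The diary-based figure that is stated, 206 per group for day 2-4 severity, reproduces on the log scale: n = 2(1.645 + 1.282)² × ln(1 + 0.7²) / (ln 1.2)² = 2 × 8.564 × 0.3988 / 0.03324 = 205.5, so 206. The duration rules do not affect it.

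**1. Open spells.** A spell must end by Day 26 for Days 27 and 28 to form the closing pair. The documents give no distribution of duration, so I assume a log-normal with control median m and log-scale SD s, and a POCT median of 1.15m. With S(t) = 1 − Φ((ln t − ln m)/s):

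- mean if open spells are excluded: [∫₀²⁶ S(t)dt − 26·S(26)] / [1 − S(26)]
- mean if they are counted to Day 28 (restricted mean): ∫₀²⁸ S(t)dt

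For m = 11 and s = 0.8, the shares open are 14.1% (control) and 18.4% (POCT). Closed-spell means are 10.73 and 11.53 days, a difference of 0.80. Restricted means are 13.15 and 14.53, a difference of 1.39 before rounding. The loss is 1 − 0.80/1.39 = 42%.

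| m, s | Open, control / POCT | Difference, excluded | Difference, counted to Day 28 | Lost |
|---|---|---|---|---|
| 8, 0.7 | 4.6% / 6.9% | 0.92 | 1.28 | 29% |
| 11, 0.8 | 14.1% / 18.4% | 0.80 | 1.39 | 42% |
| 14, 0.9 | 24.6% / 29.7% | 0.67 | 1.31 | 49% |

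Simulation with 2,000,000 draws per arm gives 0.93, 0.80 and 0.66 against 1.30, 1.39 and 1.30, the same within sampling error.

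- *Shorter illness:* with s = 0.7 the loss is 19% at a median of 6 days and 8% at 4 days.
- *Benefit instead of harm:* with the POCT median at m/1.15, the same formulas lose 24%, 39% and 47%.
- *Counting open spells to Day 28:* the mean of min(T, 28) is the restricted mean itself, so nothing is lost.

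**2. Longest spell against last day.** Take symptoms at 3 or more on days 1-3, below 3 on days 4-5, at 3 or more on days 6-7, then below 3. The SAP sees closed spells of 3 and 2 days and scores 3. The protocol's last day is Day 7. The protocol definition also gives a value (28) to a participant still moderately bad on Day 28, so for this outcome the SAP's change creates the gap.

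**3. Baseline-zero rule.** Assume a share q is below 3 at baseline, later impairment lasts 4 days, and it is 10 percentage points more common with POCT. The difference missed is q × 0.10 × 4: 0.12 days at q = 0.3 and 0.20 days at q = 0.5.

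**4. Days left blank after a permitted stop.** The two all-zero days are already the closing pair, so the durations are untouched. For day 2-4 severity, assume 10% of controls and 6% of POCT participants have recovered by Day 3, a mean of 2.3 in the rest, and within-person correlation 0.6. The true difference is 2.3 × 0.04 = 0.092. Random-intercept weights 1/(0.6 + 0.4/k) are 1.364 for three days and 1.25 for two. With Day 4 missing for the recovered, the arm means are 2.173 and 2.087, a difference of 0.0855. The shift is under 0.007, against a margin of 0.2 × 2.3 = 0.46.

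**5. Shortened six-month review.** The full window is 183 − 28 = 155 days and the shortest about 61 − 28 = 33 days. Assume 10% to 30% of participants are truncated, with follow-up spread evenly between those limits, 0.5 consultations per full window and a rate ratio of 1.3. The odds ratio for any consultation moves from 1.41 to between 1.40 and 1.39.

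**The case against.** **The SAP never says open spells are dropped.** The full analysis set is all randomised participants (SAP 3.1), the durations are typed as ordinal, and the p-value is non-parametric. A cap at Day 28 would fit all of that. This stands, and it makes the size of the loss conditional. It does not supply the missing rule, and a Day 28 cap would not settle diaries abandoned earlier.

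**Relapse and deterioration are measured elsewhere.** The relapse in the example meets the SAP's new or worsening symptoms outcome, since a symptom rises to 3 on Day 6 and is still 3 or more on Day 7. Re-consultation and admission for respiratory infection within 28 days come from medical records. This stands in part: those outcomes record that something happened, not how long it lasted.

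**The inputs are assumed.** This also stands. The documents give no duration distribution, and moderately bad symptoms cannot outlast any-symptom duration, so the shorter medians may fit that outcome better.

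**On blanks and follow-up.** A reader might infer that blank days after recovery or shortened record review distort the results. Sections 4 and 5 of the working show little effect. Truncation follows calendar time, which 1:1 randomisation should balance, and sensitivity analysis 3(ii) imputes missing day 2-4 ratings against POCT. Scoring unanswered items as zero is a prespecified convention. Averaging the answered items could overstate severity if participants rate only the symptoms they have, so I propose no change there.

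**Conclusion.** The point holds as a gap in the SAP and two unexplained departures from the protocol. The gap is certain from the text. Its effect depends on how it is filled: about 29% to 49% of a true difference lost under exclusion, for an assumed 15% prolongation and log-normal medians of 8 to 14 days; less for shorter illness; none if open spells are counted to Day 28. The longest-spell rule and the baseline-zero rule are explicit, and their effect depends on how often relapse or later impairment occurs, which the documents do not say.

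A reader might infer that the plan hides harm from fewer antibiotics. The documents do not support that: the attenuation is close to symmetric and would equally mask a benefit, and neither the primary outcome nor the day 2-4 non-inferiority test uses these durations. A reader might also take a larger loss as the headline, such as the 62% from a Weibull recovery model (shape 1.2, control median 12 days, recovery hazard ratio 0.8). None of those inputs is in the documents, and the same model loses 8% at a median of 4 days. A reader might further infer that later deterioration scores zero throughout. That is true only of return to usual activities; the longest-spell measure counts a later spell if it is the longest.

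**What to change.** Amend SAP 2.10.2, 4.7 and Table 3:

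1. Keep every randomised participant with diary data in the duration analyses. Censor open spells at the last completed diary day or Day 28. Report Kaplan-Meier curves and the 28-day restricted mean difference, adjusted for age group and chronic lung disease, beside the planned comparison of means. State that censoring at early diary stop assumes non-informative dropout.
2. Use the protocol's last-day definition for moderately bad symptoms, meaning the last diary day at or above threshold so that relapses count, or report both definitions and explain the change. Reconcile the fever condition in the usual-activities outcome at the same time.
3. For usual activities, count impairment that begins after baseline instead of assigning zero.

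Two minor tidy-ups: score symptom ratings as 0 on days after a permitted diary stop; and for consultations from 29 days to 6 months, use a count model with a log follow-up-time offset, or restrict to those fully followed.

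The cost is SAP wording and standard code on data already being collected. The one drawback is an extra estimate reported beside the mean differences.

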#### 3.2. ADVERSE EVENTS

The number of participants experiencing 0, 1, 2, or 3+ of the following events will be tabulated by allocated group: adverse events possibly, probably or definitely related to the intervention or trial procedures, all serious adverse events, serious adverse events possibly, probably or definitely related to the intervention or trial procedures, all suspected and unexpected serious adverse reactions (**Supplementary Table 7**, see Section 5). Further descriptive details will be given of any events in the latter two categories.

Note the potential overlap between adverse events, and the measure taken from the participant completed diaries “new and worsening symptoms”.

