## 6.6 Randomisation (Day 1)

### Figure 1, Step 4

Participants will be individually randomised 1:1 to intervention (GP POCTRM test) or control (No GP POCTRM test) using an internet-based randomisation system developed and maintained by Sealed EnvelopeTM. Randomisation will be stratified by age (<16 years vs. ≥16 years) and chronic lung disease (present vs. absent). It will not be possible to blind the allocated randomisation group since the subsequent processes for each group differ.

The Study Champion or Clinician randomises participants and immediately informs (if necessary) the Study Clinician which group the participant has been allocated to.

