**Table 9: Classification of Relatedness**

|                               |                                                                                                                                                                                                               |
|-------------------------------|---------------------------------------------------------------------------------------------------------------------------------------------------------------------------------------------------------------|
| Not related            | Temporal relationship of the onset of the event, relative to administration of the intervention, is not reasonable or another cause can by itself explain the occurrence of the event.                        |
| Unlikely to be related | Temporal relationship of the onset of the event, relative to administration of the intervention, is unlikely and it is likely there is another cause which can by itself explain the occurrence of the event. |
| Possibly related       | Temporal relationship of the onset of the event, relative to administration of the intervention, is reasonable but the event could have been due to another, equally likely cause.                            |
| Probably related       | Temporal relationship of the onset of the event, relative to administration of the intervention, is reasonable and the event is more likely explained by the intervention than any other cause.               |
| Definitely related     | Temporal relationship of the onset of the event, relative to administration of the intervention, is reasonable and there is no other cause to explain the event, or a re-challenge (if feasible) is positive. |

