## 9.3 Classification of (S)AEs

The PI at each site is responsible for assessing all AEs and categorising whether they are serious, expected and related to the trial procedures.

The only event expected due to the trial procedures is temporary discomfort and/or slight nose bleed from swabbing.

As is proportionate to the nature of the trial, only Suspected Unexpected Serious Adverse Reactions (SUSARs) will require expedited reporting to the Sponsor (see section 9.5.1). All other SAEs will be recorded on the SAE Summary Log (see section 9.5).

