## 9.5 Recording SAEs

Sites will record all SAEs in the SAE Summary Log in the eCRF. Data capture will be via the trial database, or in a suitable electronic format or via paper records with subsequent data entry, where necessary. The central trial team will review the SAE Summary Log regularly for monitoring and reporting purposes and will prepare regular summary reports of all SAEs for discussion at relevant oversight meetings, including with the DMC.

SAEs should also be recorded in the participant's medical notes by the site. The participant should be followed up by the site until the event resolves or a final outcome has been reached. The PI, or delegate, should complete the overall assessment. Information not available at the time must be forwarded once available.

As is proportionate to the nature of the trial, only SUSARs will require expedited reporting to the Sponsor.

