### 9.5.1 Reporting of SUSARs

Any SAEs which are assessed by the PI as being related to trial procedures and unexpected for that procedure (not listed under section 9.3) are classed as SUSARs and must be documented on the full SAE

Report Form, which is provided by the central trial team. An initial report may be provided orally but a written SAE Report Form must be completed and submitted within 24 hours of staff becoming aware of the event. Each SAE must be reported on a separate SAE Report Form. The reporting framework for SAEs is shown in Figure 4.

Any change of condition or other follow up information relating to a previously reported SUSAR will be reported on a separate SAE Follow-Up Report Form.

Sites should scan and email the SAE Report Form, with high importance, to UHBW on behalf of the Sponsor (in accordance with their SAE reporting SOP), the RAPID-TEST central trial team and copy [name] (CI), see contact details on pages 2-3.

The central trial team will confirm email receipt and if required, the Sponsor will forward the completed form to REC within the necessary reporting periods.

***NB:*** typical working hours of the central trial team (UK): Monday to Friday, 09:00-17:00 (subject to variation). In the event of University closure dates or limited availability, an out of office automatic response will notify recipients of alternative contact details/arrangements.

All SAEs will be further reported to the DMC as part of their oversight meetings. The central trial team will be responsible for all other reports to relevant regulatory authorities and trial oversight committees.

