| 3+ events                                                              | XX (XX%)            | XX (XX%)       |
| Number of suspected unexpected serious adverse reactions |                     |                |
| 0 events                                                               | XX (XX%)            | XX (XX%)       |
| 1 event                                                                | XX (XX%)            | XX (XX%)       |
| 2 events                                                               | XX (XX%)            | XX (XX%)       |
| 3+ events                                                              | XX (XX%)            | XX (XX%)       |

\*Possibly, probably or definitely related to the intervention or trial procedures

**Supplementary Table 8.** List of participants formally withdrawing from all further participation in the study

| Reason for withdrawal | Days after
randomisation |
|------------------------------|-------------------------------------|
| Intervention group    | XX                                  |
|                              | XX                                  |
|                              | XX                                  |
|                              | XX                                  |
| Comparison group      | XX                                  |
|                              | XX                                  |
|                              | XX                                  |
|                              | XX                                  |
|                              | XX                                  |

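### SAP 3.2 describes only SAEs judged related, so an SAE judged unrelated cannot be identified by arm, and no SAP text or table shell shown gives deaths by arm

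*Combined protocol and SAP*

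**What the plan says.** SAP 3.2 counts participants with 0, 1, 2 or 3+ events by allocated group in four categories, in this order: adverse events graded at least possibly related, all SAEs, SAEs graded at least possibly related, and SUSARs. It closes its first paragraph with "Further descriptive details will be given of any events in the latter two categories". Supplementary Table 7 follows the same four blocks. It has no row for death, seriousness criterion or type of event.

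Protocol 9.3 assigns the grading: "The PI at each site is responsible for assessing all AEs and categorising whether they are serious, expected and related to the trial procedures". Protocol 9.5.1 defines SUSARs as "Any SAEs which are assessed by the PI as being related to trial procedures and unexpected for that procedure". On blinding, Protocol 6.6 says "It will not be possible to blind the allocated randomisation group since the subsequent processes for each group differ".

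On data capture, Protocol 9.5 says "Sites will record all SAEs in the SAE Summary Log in the eCRF" and has each event followed until it resolves or reaches a final outcome. The other listing by arm is Supplementary Table 8, titled "List of participants formally withdrawing from all further participation in the study". SAP 4.2 also plans a CONSORT flowchart, but the figure is not reproduced in the text available.

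**The concern.** The intervention is meant to lead to fewer antibiotic prescriptions. Beyond swab discomfort, the harm of interest is a serious complication in someone who might otherwise have been treated. Such an event can reasonably be attributed to the underlying infection or to another illness, and so be judged unrelated. Under SAP 3.2 it would then carry no diagnosis, timing or outcome in the report, only a place in a count.

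Protocol 1.1 says the trial will show whether testing could safely reduce unnecessary antibiotic use. A reader checking that claim would want to know what the SAEs in each arm were and how many participants died. The rule in SAP 3.2 makes the first depend on a site judgement under open allocation. The text and shells shown do not commit to the second.

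**Working it through.** **Arm size.** Protocol 10.1.1 assumes 60% v 45%, 90% power and 5% significance (taken as two-sided). The usual two-proportion formula gives

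n = [1.960 × √(2 × 0.525 × 0.475) + 1.2816 × √(0.60 × 0.40 + 0.45 × 0.55)]² / 0.15² = 231 per group.

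The continuity-corrected form, (n/4) × [1 + √(1 + 4/(0.15n))]², gives 244, the plan's figure. Then 2 × 244 = 488, 488 / 0.95 = 513.7, rounded up to 514, and 514 / 2 = 257 randomised per arm. The concern does not rest on this figure; it only fixes the denominator.

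**What can be identified by arm.** Setting SAP 3.2 beside the table shells:

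| Event | Where it appears by arm | Identifiable? |
|---|---|---|
| Symptom severity, days 2 to 4 | SAP 4.5, Table 3 | Yes, whatever the relatedness |
| RTI admission to day 28 | Table 4 | Yes, whatever the relatedness |
| RTI consultation to day 28, and from day 29 to 6 months | Table 4 | Yes, whatever the relatedness |
| SAE graded at least possibly related, or SUSAR | Supplementary Table 7 plus description | Yes |
| SAE graded unlikely or not related, and not an RTI admission by day 28 | All-SAE block of Supplementary Table 7 only | No, count only |
| Death judged unrelated | Same all-SAE block; Supplementary Table 8 only if logged as a formal withdrawal | Not from anything shown; the CONSORT figure cannot be checked |

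The gap is the last two rows.

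**How firm the relatedness filter is.** Both described categories require a positive relatedness call, because a SUSAR is by definition an SAE judged related. Protocol Table 9 allows *not related* where "another cause can by itself explain the occurrence of the event", and *possibly related* where the timing "is reasonable but the event could have been due to another, equally likely cause". For a complication of a respiratory infection in a tested patient who was not prescribed an antibiotic, either grade can be defended: the infection can explain the event alone, and the timing is also reasonable. The choice decides whether the event is described.

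**Who makes it.** The PI does (Protocol 9.3). No sentence says that the PI knows the allocation. It is inferred from open allocation (6.6), test results filed in the intervention patients' medical notes (6.6.1), and Study Clinicians at each site being told the group (6.11).

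**Size.** The documents give no SAE or death rate, so these are assumptions. If 1%, 2% or 5% of an arm had an SAE: 0.01 × 257 = 2.6, 0.02 × 257 = 5.1 and 0.05 × 257 = 12.9, or about 3, 5 or 13 participants per arm. The SAEs left undescribed would be whichever of theirs were judged unrelated.

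A deaths row would carry little inferential weight. With no deaths among 257, the one-sided 95% upper limit for the true rate is 1 − 0.05^(1/257) = 1.16%.

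**The case against.** The best case for the plan is proportionality. All SAEs are already tabulated by arm whatever the relatedness. The outcomes most likely to reveal harm from withheld antibiotics (symptoms, RTI admissions and RTI reconsultations) are compared without any relatedness filter. The test is CE-marked, the DMC receives summaries of all SAEs, patients needing admission are excluded at entry, and the shells cover only the primary results paper. Nothing forbids reporting more. Most of this stands and is why the point is minor. But DMC review protects participants during the trial and does not put the information in the report, and freedom to report more is not a commitment to do so.

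Three stronger readings are tempting, and the documents do not support them:

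- **Deaths are left out of the plan.** A death during follow-up is ordinary content for a CONSORT flowchart, and that figure is not reproduced. Only its absence from the text and shells shown can be stated.
- **Harm from not prescribing falls outside the relatedness call.** Protocol 9.3 and 9.5.1 mention only trial procedures. SAP 3.2, Protocol 9.4 and the footnote to Supplementary Table 7 all include the intervention as well, and Protocol Table 9 judges timing against the intervention.
- **A marked imbalance in deaths is likely to lie behind equal SAE counts.** This is logically possible, but with no event rates in the documents any such split is invented. An extreme one would need every participant with an SAE in one arm to die and none in the other.

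There is also no evidence that sites would grade relatedness differently by arm. The point is that the description depends on the grade, not that the grade is biased.

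**Conclusion.** The point holds as a minor reporting weakness. SAP 3.2 sets an explicit rule that ties description of SAEs to a site relatedness call. An SAE judged unrelated and not captured as an RTI admission by day 28 therefore cannot be identified by arm. Nothing shown gives deaths by arm, subject to the CONSORT figure.

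This rests on one inference, that PIs very probably know the allocation, and on the text and shells available. No estimate, model or test changes, and the primary and key secondary conclusions are untouched. What is limited is how fully a reader can check the safety claim for deaths, for serious complications not recorded as RTI admissions, and for serious events after day 28. The number of participants involved is unknown and probably small.

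**What to change.** Replace the closing sentence of the first paragraph of SAP 3.2 with wording such as: *All SAEs will be described by allocated group, whatever the relatedness call, as grouped counts by diagnosis category, onset (to day 28 or later) and outcome. Fuller narrative will be given for related SAEs and SUSARs.* Add a *Deaths* row by group to Supplementary Table 7 unless the CONSORT figure already gives deaths by arm. Treat that row as descriptive, with no test.

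Keep the RTI-admission row of Table 4 as the main clinical safety comparison, because Protocol Table 7 does not class symptoms of the respiratory infection or treatment failure as adverse events.

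The cost is a few lines of reporting. Sites already log every SAE and follow it to an outcome. The fields of the SAE log are not shown, so some queries to sites on diagnosis, onset or outcome may be needed. Small counts carry a privacy risk; merging rare categories and avoiding per-person listings limits it but does not remove it. SAP section 1 allows amendments if they are described and justified in the final report.
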